## Abstract

**Background:**

Hypertension is currently the leading modifiable cause of global morbidity and mortality, leading to substantial health and financial burdens. Although multiple studies of management models and innovative therapeutic strategies for hypertension have been conducted, there are still gaps in the field, with a poor control rate reflecting a lack of novel, effective, clinically translated medication or intervention options. Recent animal and human studies repeatedly confirmed a link between the microbiota and hypertension. Of note is our previous study establishing a cause-and-effect relationship between the gut microbiota and blood pressure elevation. A hypothesis of gut microbiota intervention for treating hypertension is thus postulated, and fecal microbiota transplantation (FMT) from healthy donors was performed.

**Methods:**

A multicenter, randomized, placebo-controlled, blinded clinical trial will be performed in 120 grade 1 hypertensive patients for 3 months. All recruited patients will be randomly assigned in a 1:1 ratio to take oral FMT capsules or placebo capsules on day 1, day 7, and day 14 and will be followed up on day 30, day 60, and day 90. The primary outcome is the change in office systolic blood pressure from baseline to day 30. The main secondary outcomes are BP indicators, including changes in systolic and diastolic blood pressure from office and 24-h ambulatory blood pressure monitoring; assessments of ankle-branchial index and pulse wave velocity; profiling of fecal microbial composition and function; profiling of fecal and serum metabolome; changes in levels of blood glucose, blood lipids, and body mass index; and assessment of adverse events as a measure of safety.

**Discussion:**

Expanding upon our previous research on the role of the gut microbiota in the pathogenesis of hypertension, this study serves as a clinical translation advancement and explores the potential of fecal microbiota transplantation for treating hypertension. The underlying mechanisms, particularly the roles of specific microorganisms or their postbiotics in blood pressure amelioration, will also be investigated via multiple approaches, such as metagenomic sequencing and metabolomic profiling.

**Trial registration:**

ClinicalTrials.govNCT04406129. Registered on May 28, 2020

## Administrative information

Note: The numbers in curly brackets in this protocol refer to SPIRIT Checklist item numbers. The order of the items has been modified to group similar items (see http://www.equator-network.org/reporting-guidelines/spirit-2013-statement-defining-standard-protocol-items-for-clinical-trials/).

## Introduction

### Background and rationale {6a}

Cardiovascular diseases (CVDs) are currently the leading cause of global health loss, accounting for one-third of deaths worldwide [1], and it is estimated that CVDs will cause 7.8 million premature deaths in 2025 [2]. Primary hypertension is the most prevalent cardiovascular disease affecting ~ 30% of the adult population worldwide and has become a severe public health issue because of its low control rate, high morbidity rate, and involvement in ~ 19% of global deaths [3, 4]. Despite explorations on pharmacological and device-based therapies over the last 60 years, few treatment options are currently available, which stresses the importance of advances of novel hypotheses in this field.

Although blood pressure (BP) is regulated by multifactorial genetic and environmental factors, an increasing number of studies have indicated the role of the microbiota in BP homeostasis [5]. In germ-free (GF) animal models, angiotensin II (Ang II)-induced hypertension cannot be replicated [6]. Decreased diversity and discordant composition of the gut microbiota (compared to that of healthy controls) have been found in several hypertensive cohorts [7–10]. Fecal microbiota transplantation from multiple hypertensive animal models can increase BP in controls [11]. Our previous study first confirmed that transplants of hypertensive patient feces reshaped the gut microbiota of healthy GF mice and resulted in significant BP elevation [9]. Of note, modulating intestinal flora via transplantation from healthy rats could dramatically reduce BP in salt-induced hypertensive animals [12]. Oral antibiotics such as minocycline and vancomycin can assist in the treatment of hypertension [13]. Supplementary probiotics also modestly ameliorated high BP in rodents and/or humans [14–17]. A hypothesis is indeed raised that gut microbiota intervention might be a potential approach to ameliorate hypertension. Fecal microbiota transplantation (FMT) is a strategy for entire gut microbiome transplantation from healthy donors to the diseased recipient. Since 2013, FMT is recommended for treatment on recurrent Clostridium difficile infection resistant to standard-of-care therapies [18]. Potential therapeutic roles of FMT via affecting patients’ gut microbiota [19] has been examined on other gastrointestinal diseases such as inflammatory bowel disease(IBD) [20, 21] and irritable bowel disease [22], and extraintestinal diseases such as metabolic syndrome [23, 24], obese and type 2 diabetes mellitus [25, 26]. Of note, limited study of the entire gut microbial ecology restoration among hypertensive patients has been conducted, and the durability after FMT intervention remains unknown.

We herein developed a multicenter, randomized, placebo-controlled, blinded study utilizing an FMT intervention to explore the efficacy of gut microbiota intervention for the treatment of essential hypertension. We postulate that FMT intervention presents a better BP-lowering effect than placebo. Secondary outcomes also included changes in recipient fecal microbial composition and function, fecal and serum metabolome, and fasting blood glucose and lipid levels; ankle-branchial index (ABI); body mass index (BMI); and occurrence of adverse events as a measure of safety outcomes. 

### Objectives {7}

This study primarily aims to assess whether FMT ameliorates elevated blood pressure in patients with grade one essential hypertension. Additionally, this study will determine whether any BP changes are associated with alterations in the fecal microbiome and fecal and serum metabolomes of hypertensive patients when comparing these parameters measured prior to and after FMT. Of note are the microbial structure and functional alterations in the microbiota of the recipient and their durability. The durability of the clinical response after the initial response to FMT will also be evaluated in participants with hypertension. Other indicators, including fasting blood glucose and lipid levels, ABI, BMI, and occurrence of adverse events as a measure of safety outcomes, will also be assessed.

### Trial design {8}

This study is an investigator-initiated, multicenter, randomized, blinded, placebo-controlled clinical trial with a 3-month duration.

Assuming a true SBP difference between the “FMT capsule group” and “placebo group” with a mean of 5 mmHg and a standard deviation of 8.6 mmHg for SBP change per arm, a sample size of 96 grade one hypertensive patients yields > 80% statistical power to demonstrate a > 5 mmHg difference between arms at a 1-sided alpha level of 0.025. Given premature withdrawal or failure potentials before the primary end point data were collected, a 20% rate of loss-of-follow-up was calculated, resulting in the recruitment target of 120 participants with grade one hypertension who met the eligibility criteria. The participants will be randomized 1:1 to receive FMT via capsule or placebo capsules. The experimental group will then be offered three separate “FMT capsule” treatments (day 1, day 7, day 14), and the control group will then be offered three separate “placebo capsules” (day 1, day 7, day 14). In addition to the comprehensive examination before the intervention period and at the end of the trial, participants in both arms will be followed up at day 7, day 14, day 30, day 60, and day 90 to undergo an assessment of their clinical BP and other clinical indicators. Adverse events and treatment for other accompanying diseases will also be recorded at each visit, and fecal and blood samples will be collected before the trial and at each visit for future metagenomic and metabolomic profiling analysis. All staff involved in the clinical assessments, statistical analysis, and/or randomization of participants will be blinded.

The protocol report refers to the SPIRIT reporting guidelines [27].

## Methods: participants, interventions, and outcomes

### Study setting {9}

This study was conducted by Fuwai Hospital, Chinese Academy of Medical Sciences, National Center for Cardiovascular Diseases, State Key Laboratory of Cardiovascular Diseases. Patients with grade one essential hypertension will be recruited via outpatient clinics at implementation centers, including Fuwai Hospital, Chinese Academy of Medical Sciences (Beijing), Fuwai Yunnan Cardiovascular Hospital (Yunnan Province), Qilu Hospital of Shandong University (Shandong Province), the Second Affiliated Hospital of Shantou University Medical College (Guangdong Province), The People’s Hospital of Ji Xian District (Tianjin), Shanxi Bethune Hospital (Shanxi Province), and South University of Science and Technology Hospital (Shenzhen).

### Eligibility criteria {10}

The following are the inclusion criteria:
Age 18~60 yearsEstablished diagnosis of grade one hypertension (initial diagnosis or no use of antihypertensive drugs within a month): 140 mmHg ≤ office SBP < 160 mmHg and/or 90 ≤ office DBP < 100 mmHg from three measurements on different days without any antihypertensive medications, according to the “2010 Chinese Guidelines for Prevention and Treatment of Hypertension” [28].Participants who provide written informed consent after receiving a thorough explanation.

The following are the exclusion criteria:
Antibiotic or probiotic usage within one month before the studyParticipation in other clinical trials related to hypertension currently or within the last 3 monthsAntihypertensive medication usage currently or within the last monthDiagnosis of secondary hypertensionSevere hepatic or renal diseases (over 3-fold elevation of alanine transaminase, elevated serum creatinine over 2.5 mg/dl [221 μmol/L], estimated glomerular filtration rate less than 30 mL/min/1.73 m^2^, or end-stage kidney dysfunction requiring dialysis)History of stroke, including hemorrhagic stroke and large artery atherosclerotic cerebral infarction (LAACI) but not transient ischemic attack (TIA) or lacunar infarctionHistory of hospitalization within the last 6 months due to myocardial infarction, history of coronary revascularization including percutaneous transluminal coronary intervention (PCI) or coronary artery bypass grafting (CABG) within the last year, anticipated PCI or CABG surgery in the following 12 monthsSustained atrial fibrillation or arrhythmias at recruitment disturbing the electronic BP measurementNYHA class III–IV heart failure, hospitalization for chronic heart failure exacerbation within the last 6 monthsSevere valvular diseases: potential for surgery or percutaneous valve replacement within the study periodDilated cardiomyopathy; hypertrophic cardiomyopathy, rheumatic cardiac disease, congenital cardiac diseaseOther severe diseases influencing the entry or survival of participants, such as malignant tumors or acquired immune deficiency syndromeCognitive impairment or severe neuropsychiatric comorbidities, making individuals incapable of providing their own informed consentParticipants preparing for or currently experiencing pregnancy and/or lactationOther conditions deeming individuals inappropriate for recruitment according to the investigators

### Who will take informed consent? {26a}

Informed consent forms have been prepared according to the guidelines of and approved by the local ethical boards of all participating centers. The investigator or his or her designee will present the study to potential study participants and will answer study-related questions for the participants, such as study objectives, interventions, potential benefits, risks, and alternatives. The participants will read the informed consent forms and have the opportunity to communicate with their relatives prior to signing and dating the consent form. Participation in this study is voluntary and entirely up to the participants. Even if the participants do not participate, their medical services will not be affected in any way. If participants decide to participate, they also have the right to withdraw at any time and will not be influenced now or in the future regarding treatment. Once the participants decide to stop participating in the study, they will no longer be provided with the study interventions.

### Additional consent provisions for collection and use of participant data and biological specimens {26b}

Information on clinical data and fecal and blood sample collection is included in the informed consent form. The volume of fecal samples (5 g per visit) and blood samples (10 ml per visit) taken will not lead to side effects. Participation for each patient is confidential, and their identity will be confined within the study centers under participants’ agreement. To reserve options for validation and meta-analysis with future studies of FMT on hypertension, we will make our data available to other study groups after reasonable application. Coded samples may be shared with academic collaborators, including metagenomic profiles, metabolomic profiles, and clinical metadata. The sharing will be confirmed with the standard language of the informed consent, and all identifiable information will be excluded. Although current plans on potential collaboration are lacking, the options for sharing are reserved.

### Interventions

#### Explanation for the choice of comparators {6b}

According to the “2010 Chinese Guidelines for Prevention and Treatment of Hypertension”, lifestyle intervention is recommended as the first-line therapy for grade one hypertension treatment, and pharmacological interventions can be initiated after 3 months of lifestyle intervention and persistent hypertension. All participants in this study will be educated regarding lifestyle intervention and randomized to the “FMT capsule” intervention or the “placebo capsule” intervention. Participants in the “placebo capsule” group will take placebo capsules orally on day 1, day 7 (± 1 day), and day 14 (± 1 day). The placebo capsules have identically appearing powder that does not contain donor stool or any active drug.

#### Intervention description {11a}

Participants in the “FMT capsule” group will take the FMT capsules orally on day 1, day 7 (± 1 day), and day 14 (± 1 day). The FMT capsules (China National Intellectual Property Administration, patent ID. CN 104922158 B) are prepared by processing extensively screened donor stool in reference to the current consensus on FMT [19, 29–31] and stored at − 80 °C in freezers before recovery for use. Light, high-liquid meals on the day before intervention and fasting for at least 4 h prior to and 2 h after intervention are required.

#### Criteria for discontinuing or modifying allocated interventions {11b}

The discontinuation criteria include withdrawal of informed consent, loss to follow-up, occurrence of serious adverse events, complications, certain physiological changes or other medical reasons precluding continuation of the study according to the investigators’ assessment, and significant deviation from the intervention algorithm, which would probably affect the outcome evaluation of the study.

#### Strategies to improve adherence to interventions {11c}

Before inclusion, the willingness to comply will be repeatedly confirmed among potential participants. An advantage in regard to compliance is that all capsules are taken at three intervention visits within two weeks. The FMT capsules and placebo capsules will be stored, delivered, and recovered by investigators and/or patient care providers from the implementation centers. All capsules will be stored in − 80 °C freezers and delivered from the trial center into implementation centers via dry ice. Before the intervention, the investigators and/or patient care providers will recover capsules in a 37 °C water bath and make detailed records of the number of distributed, administered, and returned capsules. All recovered capsules at each visit will be orally taken within 30 min under clinical supervision. The remaining study capsules will be returned to the responsible center. The participant compliance rate will be evaluated as the actual number of capsules used divided by the anticipated number of capsules used × 100%. Good compliance is defined as a compliance rate of 80–120%; poor compliance is defined as a compliance rate less than 80% or more than 120%. If poor compliance is identified, thorough communication between investigators and patients will be performed to reach possible solutions. In addition, an assessment of the gut microbial composition between FMT capsules and stool samples from recipients at different time points will be performed to assess the engraftment of microbiota, which will provide additional information regarding participant adherence in part.

#### Relevant concomitant care permitted or prohibited during the trial {11d}

In reference to the hypertension guidelines, lifestyle modifications are recommended for all hypertensive patients and for all participants recruited in this study. During the treatment and follow-up period, participants will be asked to maintain a routine pattern of daily activities, such as physical activity, lifestyle, and habits. To minimize the interference caused by dietary environmental factors on the intestinal flora, recruited participants in each arm will be required to record their dietary history before each study visit and to make no dietary habit changes throughout the trial. Antihypertension medications and the use of probiotics, prebiotics, or antibiotics will be avoided during the study period except for in specific clinical conditions (i.e., persistent BP elevation over 180/110 mmHg) requiring pharmacological interventions on the basis of the physician’s evaluation. The conventional treatment for accompanying diseases in participants can remain unchanged and will be recorded. Treatment for adverse events is permitted and will be recorded.

#### Provisions for post-trial care {30}

In accordance with the informed consent form, appropriate medical care and assistance will be provided rather than direct financial compensation for participants who suffer harm relevant to trial participation. Additionally, close monitoring and management will be performed for those participants according to relevant laws and regulations.

### Outcomes {12}

Our primary hypothesis is a BP-lowering effect of gut microbiota restoration via FMT compared to the effects observed in the placebo group in grade one hypertensive patients. Accordingly, the primary outcome is defined as the change in office systolic blood pressure (SBP) level from baseline to the one-month follow-up (day 30).

Other indicators related to BP evaluation, safety concerns, and potential mechanism exploration will be assessed as the main secondary outcomes and include the following:
Change in office systolic blood pressure (SBP) level via office BP monitoring from baseline to day 7, day 14, day 60, and day 90 visitsChange in office diastolic blood pressure (DBP) level via office BP monitoring from baseline to day 7, day 14, day 30, day 60, and day 90 visitsChange in average SBP and DBP during the 24-h assessment, day, and night via 24-h ambulatory BP monitoring (ABPM) from baseline to day 30 and day 90 visitsTarget organ damage assessment from baseline to the final visit (day 90 visit), including (a) the change in ankle-brachial blood pressure index (ABI) as an objective measurement of arterial insufficiency based on the ratio of ankle systolic pressure to brachial systolic pressure and (b) the change in pulse wave velocity as the distance divided by the time for a pulse delay between two arterial sitesNumber of participants with adverse events (AEs) documented CRF as a measure of safety at baseline, day 7, day 14, day 30, day 60, and day 90 visitsChanges in fecal microbiota composition and function pre- and postintervention (FMT or placebo) via metagenomic analysis, stratified by (a) randomization and (b) change in office SBP level from baseline to day 7, day 14, day 30, day 60, and day 90 visitsDurability of engraftment of donor microbiome following FMT to day 7, day 14, day 30, day 60, and day 90 visits, measured by the similarity of fecal microbiota composition between donor and recipientChanges in fecal metabolite composition and function pre- and postintervention (FMT or placebo) via metabolomic analysis, stratified by (a) randomization and (b) change in office SBP from baseline to day 7, day 14, day 30, day 60, and day 90 visitsChanges in blood metabolite composition and function pre- and postintervention (FMT or placebo) via metabolomic analysis, stratified by (a) randomization and (b) change in office SBP level from baseline to day 7, day 14, day 30, day 60, and day 90 visitsChange in fasting blood glucose levels from baseline to the final visit (day 90 visit)Change in blood lipid levels (total cholesterol, total triglycerides, low-density lipoprotein cholesterol, and high-density lipoprotein cholesterol) from baseline to the final visit (day 90 visit)Change in body mass index from baseline to the final visit (day 90 visit)

#### Participant timeline {13}

The participant timeline is presented in Table 1.

**Table 1 Tab1:** The schedule of enrollment, interventions, and assessments

Workflow	***Enrollment***	***Allocation***	***Follow-up***					***Close-out***
	***− 7 days***	***Day 0***	***Day 1***	***Day 7***	***Day 14***	***Day 30***	***Day 60***	***Day 90***
**Enrollment**								
***Eligibility screening***	✓							
***Informed consent***	✓							
***Allocation***		✓						
**Interventions**								
***FMT capsules***			✓	✓	✓			
***Placebo capsules***			✓	✓	✓			
**Assessments**								
***Comorbid diseases and treatment***	✓							
***Physical examination***	✓							✓
***Office BP and heart rate***	✓			✓	✓	✓	✓	✓
***24-h ABPM***	✓					✓		✓
***Blood routine***	✓							✓
***Urine routine***	✓							✓
***Blood chemical test***	✓							✓
***Urine microalbumin, creatinine***	✓							✓
***ECG***	✓							✓
***Arterial stiffness (ABI, PWV)***	✓							✓
***Diet records***			✓	✓	✓	✓	✓	✓
***Patient compliance***			✓	✓	✓			
***Adverse events***			✓	✓	✓	✓	✓	✓
***Combined medications for accompanied diseases***			✓	✓	✓	✓	✓	✓
***Fecal sample collection***	✓			✓	✓	✓	✓	✓
***Blood sample collection***	✓			✓	✓	✓	✓	✓

Blood biochemical test: *ALT* alanine aminotransferase, *AST* aspartate aminotransferase, *K* potassium, *Na* sodium, *Cl* chloride, *BUN* urea nitrogen, *CREA* creatinine, *UA* uric acid, *TC* total cholesterol, *TG* triglyceride, *HDL-C* high-density lipoprotein cholesterol, *LDL-C* low-density lipoprotein cholesterol, *GLU* fasting blood glucose

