### Data collection and management

#### Plans for assessment and collection of outcomes {18a}

All outcomes will be evaluated at seven time points, including baseline, the first intervention day, and 7 days, 14 days, 30 days, 60 days, and 90 days after intervention initiation. In addition to the kick-off meeting on February 26, 2021, all staff involved in the study were trained on a detailed study protocol, participant recruitment and informed consent, clinical assessment, sample collection and storage, and data collection utilizing printed CRFs and EDC systems.

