#### The week prior to enrollment (− 1~0 week)

The following procedures will be completed:
Written informed consent will be obtained from the participants for the study, and the screening questionnaire will be completed.Office blood pressure and heart rate will be recorded.Previous history, current and prior treatment, and other documented eligibility factors will be recorded.Personal information such as height, weight, and waist circumference will be recorded.Examinations including 24-h ABPM, electrocardiography, routine blood tests, blood biochemical tests, routine urine tests, urine microalbumin, creatinine, and arterial stiffness assessments (PWV, ABI) will be performed.Participant eligibility will be reconfirmed according to the inclusion and exclusion criteria.The baseline case report form (CRF) with printed CRF and EDC system will be completed.Fecal and blood samples will be collected.The appointment for the randomization visit will be made (within a week after screening).

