#### Randomization (day 0)

Participants will be randomly assigned to receive the first capsule treatment (day 1), and a dietary history will be collected before treatment.

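### Table 1 schedules no office BP between screening week and day 7, while the outcome-collection text lists the first intervention day; reconcile them and use a better baseline to recover modest precision

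*Protocol article*

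**What the plan says.** Outcomes {12} defines the primary outcome as the change in office SBP from baseline to day 30. Statistical methods {20a} analyses it by ANCOVA adjusting for baseline SBP and center, so baseline SBP is used both in the change score and as a covariate.

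In Table 1 the row "Office BP and heart rate" has ticks at −7 days and at days 7, 14, 30, 60 and 90. The cells for day 0 and day 1 are empty. The visit descriptions agree with the table:

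- The week prior to enrollment: "Office blood pressure and heart rate will be recorded".
- Randomization (day 0): allocation, and "a dietary history will be collected before treatment". No blood pressure is listed.
- Treatment period: adherence, adverse events, treatment of comorbidities and diet.
- Follow-up visits: office BP is recorded from day 7.

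The section on plans for assessment and collection of outcomes {18a} differs: "All outcomes will be evaluated at seven time points, including baseline, the first intervention day, and 7 days, 14 days, 30 days, 60 days". The list closes with day 90. It counts the first intervention day separately from baseline.

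Eligibility {10} requires grade one hypertension "from three measurements on different days without any antihypertensive medications", met on SBP and/or on DBP.

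**The concern.** The schedule and the text disagree on whether office SBP is measured on the day of the first capsules. A site that follows {18a} would record a pre-dose value and a site that follows Table 1 would not, so the value available as baseline could differ between centers.

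If Table 1 governs, the only protocol-timed office SBP before dosing comes from the screening week, when eligibility is confirmed. A value tied to an entry threshold tends to fall at the next measurement without any treatment. Two uses of the data are exposed to this: the before-and-after comparisons named in Objectives {7}, and the microbiome and metabolome outcomes stratified by change in office SBP in Outcomes {12}. Patients placed in a large-fall stratum will partly be those whose baseline happened to read high.

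A baseline from fewer readings is also a noisier ANCOVA covariate and removes less variance from the primary comparison.

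**Working it through.** **1. Count of time points for office SBP.** Table 1: −7 days and days 7, 14, 30, 60, 90, which is six. Section {18a}: baseline, first intervention day and days 7, 14, 30, 60, 90, which is seven. The difference is the first intervention day.

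**2. The plan's own sample size.** Inputs from Sample size {14}: difference 5 mmHg, SD of change 8.6 mmHg, one-sided alpha 0.025, power 80%.

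n per arm = 2 × (1.960 + 0.842)² × 8.6² / 5² = 46.4, so 47 per arm (94 in total) by the normal approximation. With the t distribution, power is 79.6% at 47 per arm and 80.5% at 48, which gives 96. Then 96 / 0.8 = 120. The stated figures reproduce.

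**3. Precision from a second baseline reading.** The documents give no correlation between visits, so ρ = 0.3 to 0.7 is assumed, equal between all pairs of readings. Holding the SD of change at 8.6, the variance of one reading is s² = 8.6² / [2(1 − ρ)]. With the mean of k baseline readings as covariate, the ANCOVA residual variance is s² × [1 − kρ² / (1 + (k − 1)ρ)]. Power is for 5 mmHg, 48 per arm and 93 degrees of freedom, ignoring center terms and selection.

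| ρ | SD of one reading | Residual SD, k = 1 | Power | Residual SD, k = 2 | Power |
|---|---|---|---|---|---|
| 0.3 | 7.27 | 6.93 | 93.8% | 6.75 | 94.9% |
| 0.4 | 7.85 | 7.20 | 92.1% | 6.90 | 94.0% |
| 0.5 | 8.60 | 7.45 | 90.2% | 7.02 | 93.2% |
| 0.6 | 9.62 | 7.69 | 88.3% | 7.13 | 92.5% |
| 0.7 | 11.10 | 7.93 | 86.4% | 7.23 | 91.8% |

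The gain is 1.1 to 5.4 points. In residual variance, the ratio of k = 2 to k = 1 is 0.8615 / 0.91 = 0.947 at ρ = 0.3 and 0.4235 / 0.51 = 0.830 at ρ = 0.7, a reduction of 5% to 17%.

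**4. Regression to the mean and bias.** This was simulated with 2,000 trials per setting and 48 per arm. Assumptions: population SBP mean 142 and SD 12, ρ = 0.5, and every patient selected on SBP of 140 to below 160.

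| Baseline used | Placebo-arm change | ANCOVA estimate, true 0 | ANCOVA estimate, true −5 | One-sided type I error |
|---|---|---|---|---|
| One reading, which qualified the patient | −3.1 | −0.08 | −5.10 | 0.024 |
| Last of three readings that all qualify | −1.7 to −1.8 | 0.04 | −5.01 | 0.0275 |
| Mean of three readings that all qualify | −1.8 | 0.01 | −5.04 | 0.028 |
| Separate reading after selection | about 0 | 0.07 | −5.01 | 0.0225 |

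The Monte Carlo standard error of the type I error is √(0.025 × 0.975 / 2000) = 0.0035, so all four values are compatible with 0.025. Against the 5 mmHg target, a placebo-arm fall of 1.8 to 3.1 mmHg is 36% to 62%. The assumed SD is larger than the plan implies at this correlation, so only the comparison between rows is informative.

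**The case against.** The strongest reply is that only one sentence is out of step. "All outcomes" in {18a} cannot be literal, because Table 1 schedules ambulatory monitoring, arterial stiffness and laboratory tests at far fewer visits, and Outcomes {12} lists no day-1 blood pressure. This is fair: the sentence is probably summary wording. It still has to be corrected, because it concerns the primary variable.

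A reader might go further and infer that baseline is the single reading that qualified the patient, and that the primary comparison is therefore unsound. The documents do not support that. The article does not say which reading, or which average, is baseline; the full protocol or analysis plan may do so. Qualification uses three measurements on different days, which limits selection and noise, and some patients enter on DBP alone, so SBP selection does not apply to everyone. A baseline taken before allocation is correct practice. Nor can it be argued that screening BP precedes the lifestyle education, since its timing is not stated.

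It is also true that power is not short of plan. The sample size used the unadjusted SD of change, and ANCOVA with one baseline reading already gives 86% to 94% under the assumed correlations. The omics outcomes are also stratified by randomization, so the placebo arm shows how much regression there is.

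Finally, Trial status reports 120 participants recruited by 16 September 2021, so a day-1 measurement can no longer be added for them. This stands and limits the fix to what was recorded and to the analysis.

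**Conclusion.** The inconsistency between Table 1 with its visit descriptions and section {18a} is real and needs reconciling. It does not threaten the primary comparison: the between-arm ANCOVA estimate is unbiased, type I error is near nominal in the simulation, and 96, 120 and power above 80% all stand.

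Two modest consequences remain. The first is precision: about 1 to 5 power points forgone relative to a two-reading baseline, if the between-visit correlation is 0.3 to 0.7 and one office reading would otherwise serve as baseline. The entry range narrows the spread of SBP, which makes the lower end more plausible. If the full plan already averages several screening readings, the gain is smaller still.

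The second is interpretation: within-arm falls, and strata formed on SBP change, can carry regression to the mean. The simulated 1.8 to 3.1 mmHg depends on the assumed population and on selecting everyone by SBP, so it indicates the order of size and is probably high for this trial.

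**What to change.** 1. Reconcile {18a} with Table 1. State whether office SBP was taken on day 1 before the first capsules, and make the table and the visit descriptions say the same.
2. If a day-1 pre-dose office SBP is available for all participants, define baseline SBP, for both the change score and the ANCOVA, as the mean of the screening and day-1 pre-dose values. This would roughly halve the regression in the within-arm change: in the single-reading simulation, from 3.1 to about (3.1 + 0) / 2 = 1.6 mmHg.
3. Otherwise, before database lock, pre-specify the screening 24-h ambulatory mean SBP as an additional baseline covariate in the primary ANCOVA. Table 1 already schedules it for everyone. Its gain cannot be quantified, because the documents give no correlation between office and ambulatory SBP. It helps precision only and does not remove regression from within-arm changes.
4. Do not interpret within-arm changes from baseline, or results by stratum of SBP change, as treatment effects without the placebo comparison.

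The cost is a few sentences of protocol and analysis wording before lock. The downsides are one extra covariate if step 3 is used, and slightly smaller reported within-arm falls if step 2 is used. In a future trial, a pre-dose reading would cost a few minutes at a visit that already takes place.
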